#### Economic evaluation

We will perform an economic analysis from a healthcare perspective alongside the clinical trial. We make a distinction between direct costs and indirect costs. Direct costs include the costs of medication, cycle monitoring, interventions and the costs of pregnancy leading to live birth. Indirect costs are collected from the individual case report forms of the RCT. For each woman, we registered cycle monitoring (number of ultrasounds), we registered the medication and interventions (cycles with IUI, cycles with ICI) they received within six subsequent cycles or until an ongoing pregnancy occurred within a time horizon of 8 months.

Societal costs of travel and time will be determined on basis of recourse use as registered in the case report form.

We will analyse a cost-minimisation or cost-effectiveness analysis depending on the outcome of ongoing pregnancy rates in both groups. We present the cost-effectiveness of each strategy as cost per ongoing pregnancy and costs per live birth. We explore the robustness of the results for various assumptions and parameter estimates in sensitivity analysis outcomes and we express these in incremental cost-effectiveness ratio graphs and cost-effectiveness acceptability curves. The economic evaluation will be reported in a separate paper.

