#### Power calculation

The study is designed as a non-inferiority trial. We assume that six cycles can be completed within a fixed time horizon of 8 months. Assuming a live birth rate of 40% after six cycles of IUI, we need 208 women per arm with an alpha of 0.05, and a beta of 0.80 to demonstrate the non-inferiority of ICI with a margin of 12%.^7^

The margin of 12% are the differences shown in literature between IUI and ICI.^3^

A limitation of our study is that we use a non-inferiority margin of 12%. Most clinicians and patients would feel that 12% is a rather large and clinically relevant difference.

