#### Data analysis

We will compare baseline measurements female age, body mass index, indication for AID, previous assisted reproductive treatments, previous pregnancies, parity, intoxication and referral status.

The analysis of all outcomes is on an intention-to-treat basis. For ongoing pregnancy we will test non-inferiority on basis of the absolute risk difference with the absolute margin of 12%. We will subsequently estimate differences in the primary and secondary outcomes as relative risks with 95% CI. We will also report p values.

We will evaluate association and interaction with our primary outcome of baseline variables in logistic regression analyses. The baseline variables that we plan to include in these analyses are timing, sperm quality and practice variation.

We will construct Kaplan-Meier survival curves for time to ongoing pregnancy.

For continuous variables, we examine the distribution of the observations, and if normally distributed, we summarise them as means with SDs. If they are not normally distributed, medians and IQRs are reported. For dichotomous data, we provide proportions (or percentages). In addition to the baseline and outcome data, we also summarise the recruitment numbers, those lost to follow-up, protocol violations and other relevant data. We will analyse a maximum of six cycles of IUI or ICI performed within a time horizon of eight months after randomisation.

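### The economic evaluation lets the observed pregnancy rates decide between cost-minimisation and cost-effectiveness, so a real difference in pregnancies could drop out of the analysis

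*Protocol article*

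**What the plan says.** All the economic text is in the Economic evaluation section of the protocol article.

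- Type of analysis: "We will analyse a cost-minimisation or cost-effectiveness analysis depending on the outcome of ongoing pregnancy rates in both groups". The text does not say whether the deciding result is a non-inferiority verdict, a non-significant test or something else.
- Outputs: the next sentence reads "We present the cost-effectiveness of each strategy as cost per ongoing pregnancy and costs per live birth". After sensitivity analyses are mentioned, it adds "we express these in incremental cost-effectiveness ratio graphs and cost-effectiveness acceptability curves". Neither statement is limited to one branch of the choice.
- Perspective: "We will perform an economic analysis from a healthcare perspective alongside the clinical trial".
- Costs: direct costs are listed and include those of pregnancy leading to live birth. Then "Indirect costs are collected from the individual case report forms of the RCT", and in a separate paragraph "Societal costs of travel and time will be determined on basis of recourse use as registered in the case report form".

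Two other sections set the scale. Data analysis says "For ongoing pregnancy we will test non-inferiority on basis of the absolute risk difference with the absolute margin of 12" per cent. Power calculation gives 208 women per arm, "Assuming a live birth rate of 40% after six cycles of IUI", and concedes that a 12% difference would seem large and clinically relevant to most clinicians and patients.

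**The concern.** Cost-minimisation is valid only when the effects can be taken as equal. Here the method is chosen after the pregnancy rates are known, and the results most likely to lead to it do not establish equality. A non-inferiority verdict says that the loss with ICI is probably smaller than 12 points. A non-significant difference says only that zero is not excluded. If either were read as permission to compare costs alone, the estimated difference and its confidence interval would leave the economic analysis just when the trade-off between cost and pregnancies needs to be shown.

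The rule also does not fit the rest of its own section. Incremental ratios and acceptability curves need an effect difference, so a pure cost-minimisation cannot produce them. Either the switch or the unconditional list of outputs must give way.

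The second and smaller issue is the cost base. A healthcare perspective does not ordinarily include patients' travel and time, and the protocol itself calls these costs societal.

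What is at stake is the economic conclusion. The Introduction justifies the trial by the possibility that IUI costs more for no gain in pregnancies, so that conclusion will carry weight.

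**Working it through.** **Inputs.** From Power calculation: 208 per arm, IUI rate 40%, margin 12 points, alpha 0.05 with sidedness not stated, and 80% power (written as a beta of 0.80). Assumption: for the sample size, the ICI rate equals the IUI rate, since the text gives no ICI rate. The 40% is stated for live birth and is used here for ongoing pregnancy too, because the primary outcome links the two.

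**Step 1: reproduce the plan's figure.** n per arm = (z_alpha + z_power)² × 2 × 0.40 × 0.60 / 0.12².

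- One-sided 5%: (1.645 + 0.842)² × 0.48 / 0.0144 = 206.1, so 207, against 208 stated.
- One-sided 2.5%: (1.960 + 0.842)² × 0.48 / 0.0144 = 261.6, so 262.

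A one-sided 5% comparison of 40% with 28% with continuity correction gives 208 exactly. Both matching routes are one-sided 5%, but this is inferred. Results are shown for both levels.

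**Step 2: largest observed deficit that still passes non-inferiority.** Solve d + z × SE(d) = 0.12, where SE(d) = √{[0.40 × 0.60 + (0.40 − d)(0.60 + d)] / 208} and IUI is observed at 40%.

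- One-sided 5%: at d = 0.0418, SE = 0.0475 and 0.0418 + 1.645 × 0.0475 = 0.120. The deficit is 4.2 points, about 42 per 1000 women. With both rates fixed at 40% in the SE, 0.12 − 1.645 × √(0.48/208) = 0.041, nearly the same.
- One-sided 2.5%: at d = 0.0264, SE = 0.0477 and 0.0264 + 1.960 × 0.0477 = 0.120. The deficit is 2.6 points, about 26 per 1000.

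**Step 3: largest observed deficit that is not significant (two-sided 5%).** Solve d = 1.96 × √{2p(1 − p)/208} with p = 0.40 − d/2. At d = 0.092, p = 0.354 and the right side is 1.96 × 0.0469 = 0.092. The deficit is 9.2 points, about 92 per 1000.

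**Step 4: how often a true deficit would meet each possible trigger.** P(non-inferior) = Φ{(0.12 − d)/SE(d) − z}. P(not significant) = Φ{1.96 − d/SE(d)} − Φ{−1.96 − d/SE(d)}. For d = 0.06, SE = 0.0473. The first at one-sided 5% is Φ(1.27 − 1.645) = 0.35, and the second is Φ(0.69) − Φ(−3.23) = 0.75.

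| True ICI deficit | Non-inferior, one-sided 5% | Non-inferior, one-sided 2.5% | Not significant, two-sided 5% |
|---|---|---|---|
| 4 points | 51% | 39% | 87% |
| 6 points | 35% | 25% | 75% |
| 8 points | 21% | 13% | 60% |
| 12 points | 5% | 2.5% | 26% |

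So a real loss of several points could well satisfy either trigger.

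**Step 5: perspective.** No arithmetic applies. One sentence declares a healthcare perspective. Later sentences in the same section gather indirect costs and travel and time costs, which the text labels societal. Nothing says whether these enter the main cost difference or are reported apart.

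**The case against.** The strongest reply is that the effect-based outputs are promised without condition. Cost per ongoing pregnancy, cost per live birth, ratio graphs and acceptability curves follow directly after the switch, and the Introduction likewise announces a cost-effectiveness analysis with no proviso. On that reading lost pregnancies stay visible whatever the result. This stands in part: valuing a loss at zero is a risk and not a certainty. But it leaves the switch with no role, which is a reason to delete it.

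It can also be said that the article condenses a fuller protocol, that the trigger may be defined there, and that the evaluation goes into a separate paper. The missing threshold is therefore not the complaint. The complaint is the stated rule, which remains unsound under either natural trigger.

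A reader might infer more than the text supports:

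- That the answer is fixed in advance in favour of ICI. The Introduction reports IUI costs estimated at four times those of ICI, but this comes from a cited source. The trial's cost base also includes medication, monitoring and pregnancy costs, and monitoring is the same in both arms. No total cost ratio per woman is given.
- That ICI would be favoured whatever number of births is lost, or that 120 births per 1000 would be valued at zero. Twelve points is the limit that the confidence bound must not cross, not an estimate of loss. Under a non-inferiority trigger the observed deficit cannot exceed about 4 points, and a true 12-point loss would pass only 5% of the time (2.5% at the stricter level).
- That societal costs are added into the healthcare ratio. The text says only that they will be determined. Separate reporting is a possible reading, so this part is an inconsistency of labelling.

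**Conclusion.** The point holds as a flaw in a stated analysis rule. Choosing cost-minimisation because of the observed pregnancy rates would rest on a result that does not show equal effect, and it conflicts with outputs planned in the same section. If non-inferiority is the trigger, an observed ICI deficit of up to 2.6 to 4.2 points, or about 26 to 42 fewer pregnancies per 1000 women, could be treated as no difference. If non-significance is the trigger, the figure is about 9 points. These sizes assume 208 women per arm and an IUI rate of 40%; the trigger itself is an assumption, and one-sided 5% is inferred from the stated sample size. Whether the loss would in fact be ignored depends on how the section is followed. The mixed perspective is a lesser matter. Neither part touches the primary clinical conclusion.

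**What to change.** Delete the sentence that makes the type of analysis depend on the pregnancy rates. State instead that incremental cost and incremental effect will always be estimated jointly, with their uncertainty, and shown on the cost-effectiveness plane and acceptability curve already planned, whatever the non-inferiority result. The cost difference alone can still be read from that analysis.

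For the perspective, say how travel and time costs and the indirect costs relate to the healthcare perspective. One workable form keeps healthcare costs as the stated perspective and reports travel and time in a separately labelled societal analysis.

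The cost is a change of wording and a small amount of analysis work. No further participants or data are needed, because the case report forms already supply the cost items and the planned curves already require the joint analysis.

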## Introduction

Artificial insemination with donor sperm (AID) may be performed in heterosexual couples for medical reasons or to assist lesbian couples or single women to achieve pregnancy. Medical reasons for AID include obstructive and non-obstructive azoospermia, severely impaired semen quality in couples who do not wish to undergo or were not successful with intracytoplasmatic sperm injection (ICSI), severe rhesus iso-immunisation, prevention of vertical transmission of a genetic defect or prevention of transmission of HIV in couples who do not wish to undergo semen washing.^1 2^ Women can be inseminated via the intrauterine (IUI) or the intracervical (ICI) route with or without ovarian stimulation.

A systematic review, in women who started AID, reported IUI with ovarian stimulation (IUI-OS) to be more effective than ICI-OS in terms of live birth rate (OR 2.55, 95% 0.72 to 8.96, 1 RCT, n=43) and clinical pregnancy rate (OR 2.83, 95% CI 1.38 to 5.78, 2 RCTs, n=131) at the cost of a higher multiple pregnancy rate (OR 2.77, 95% CI 1.00 to 7.69, 2 RCTs, n=131). In women who started AID in the natural cycle, IUI resulted in similar live birth rates as ICI in the natural cycle (OR 3.24, 95% 0.12–87.13, 1 RCT, n=26) but in higher clinical pregnancy rates in (OR 6.18, 95% CI 1.91 to 20.03, 2 RCTs, n=76). There were no multiple pregnancies.^3^

Multiple pregnancies are associated with increased perinatal and maternal morbidity and perinatal mortality and are regarded as an adverse treatment outcome that is no longer acceptable and should be prevented.^4–6^

Therefore, the single existing guideline on AID, published by The Royal College of Obstetrics and Gynaecology, recommends six cycles of IUI in the natural cycle.^1^

In 2012, we performed a retrospective nationwide cohort study among eight sperm banks in the Netherlands on IUI and ICI in the natural cycle. We included 1843 women of whom 1163 underwent 4269 cycles of IUI in the natural cycle and 680 underwent 2345 cycles of ICI in the natural cycle. Cumulative ongoing pregnancy rates over six treatment cycles were 40.5% for IUI and 37.9% for ICI, resulting in an HR of 1.02 (95% CI 0.84 to 1.23) for IUI versus ICI.^7^

The costs for IUI have been estimated to be four times higher than ICI, mostly because of the sperm processing inherent to IUI.^8^

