Since evidence that underpins the superiority of IUI in the natural cycle over ICI in the natural cycle is scarce and IUI may generate higher costs than ICI for no increase in pregnancies, we propose a multicentre trial comparing IUI and ICI in the natural cycle with a cost-effectiveness analysis alongside the trial.

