#### Interventions

In the IUI cycles, ovulation detection is performed with Luteinising Hormone (LH) tests or by transvaginal sonography, depending on the local setting. In case of monitoring with urinary LH tests, women test their urine once per day, starting on an individually calculated cycle day based on their basal body temperature chart. Women are inseminated with processed semen the day after the endogenous LH surge has been detected in the urine sample. Serum LH measurements are performed from day 11 of the menstrual cycle onwards and women are inseminated 1 day after the serum LH rise.^9^ In case follicular growth is monitored by transvaginal sonography, timing of insemination can be performed by ovulation triggering or by measuring serum LH levels. In case of ovulation triggering human chorionic gonadotropin (Pregnyl, Organon, Oss, The Netherlands) is administered when the dominant follicle has a diameter of at least 16 mm. Women are inseminated 36 to 40 hours thereafter. The semen may be processed in two ways. One way is to process the semen against a density gradient centrifugation and/or a washing step with culture medium according to local laboratory protocol after thawing of the—unprocessed—cryopreserved semen and the second way is to process the semen against a density gradient centrifugation and/or washing step with culture medium according to local laboratory protocol before freezing of the semen. In the ICI cycles, ovulation detection is in the same way as in the IUI arm and insemination is also timed identical to the IUI arm. Women are inseminated with unprocessed semen once per cycle, and preferably by a cervical cap.^6^ Before starting a new treatment cycle with IUI or ICI, women undergo a pregnancy test (Human gonadotrophin hormone (hCG) measurement in serum or urine). If the woman is not pregnant the next treatment cycle is started according to protocol. In case of a positive pregnancy test, women are monitored by transvaginal sonography. Monitoring will take place at 5 to 9 weeks of amenorrhoea to check whether an intrauterine gestational sac is present, that is, a clinical pregnancy.

Subsequently, monitoring takes place at 11 to 12 weeks amenorrhoea to register the presence of an intrauterine gestational sac with fetal heartbeat, that is, an ongoing pregnancy.

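### The stated cost-effectiveness measure is an average ratio per arm; the incremental cost per extra pregnancy or live birth should be the base-case result (minor)

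*Protocol article*

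**What the plan says.** The Introduction motivates the economic work by comparing the two options: "IUI may generate higher costs than ICI for no increase in pregnancies". It also gives a cost relation, "The costs for IUI have been estimated to be four times higher than ICI", and attributes it mostly to sperm processing.

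The Economic evaluation section then sets out three steps.

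- The type of analysis is chosen from the results: "We will analyse a cost-minimisation or cost-effectiveness analysis depending on the outcome of ongoing pregnancy rates in both groups".
- The measure is stated by strategy: "We present the cost-effectiveness of each strategy as cost per ongoing pregnancy and costs per live birth".
- Robustness to assumptions is explored in sensitivity analyses, and "we express these in incremental cost-effectiveness ratio graphs and cost-effectiveness acceptability curves".

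Costs are broad: "Direct costs include the costs of medication, cycle monitoring, interventions and the costs of pregnancy leading to live birth". No economic measure is labelled primary. The section says that the evaluation will be reported in a separate paper.

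**The concern.** Cost per ongoing pregnancy for a strategy is that arm's total cost divided by that arm's pregnancies. A woman receives one strategy or the other, so the decision turns on what IUI adds to cost and what it adds to pregnancies. Two within-arm averages do not contain that quantity. A reader who sets them side by side will tend to rank the arms, and the ranking can favour the cheaper arm even when it produces clearly fewer pregnancies. When the rates are close, the IUI average also gives no sign of how expensive each additional pregnancy is.

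The incremental displays are planned. On the natural reading, however, they attach to the sensitivity analyses, which leaves the per-arm averages as the stated base case. At stake is how the separate economic paper presents and interprets its main result. The clinical analysis is not affected.

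**Working it through.** **The plan's own figures.** The article gives no economic figure for either arm, so there is none to reproduce. The rates come from the Power calculation: "Assuming a live birth rate of 40% after six cycles of IUI, we need 208 women per arm", with a 12-point margin. They agree with the stated sample size: 2 × 0.40 × 0.60 × (1.645 + 0.842)² / 0.12² gives 207 per arm at one-sided alpha 0.05 and 80% power, against the stated 208. So 40% and 28% are the plan's own reference points.

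**Formulas.** Let c be the cost per woman with ICI, R the all-in IUI:ICI cost ratio per woman, and p the pregnancy rate in each arm.

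- Average, ICI: c / p(ICI)
- Average, IUI: R·c / p(IUI)
- Incremental cost per extra IUI pregnancy: (R − 1)·c / [p(IUI) − p(ICI)]
- ICI has the lower average whenever R > p(IUI) / p(ICI)

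**At the margin limit (40% and 28%).** The threshold is R = 0.40/0.28 = 1.43. The ICI average is c/0.28 = 3.6c throughout.

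| R (assumed) | IUI average | Lower average | Cost per extra IUI pregnancy |
|---|---|---|---|
| 4 | 4c/0.40 = 10c | ICI | 3c/0.12 = 25c |
| 2 | 2c/0.40 = 5c | ICI | 1c/0.12 = 8.3c |
| 1.5 | 1.5c/0.40 = 3.75c | ICI | 0.5c/0.12 = 4.2c |
| 1.25 | 1.25c/0.40 = 3.1c | IUI | 0.25c/0.12 = 2.1c |

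**How far the ranking tolerates a loss.** With IUI at 40%, break-even for ICI is 0.40/R, a proportional loss of 1 − 1/R: 10% (75% lost) at R = 4, 20% (50% lost) at R = 2, and 26.7% (33% lost) at R = 1.5.

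**At the cohort rates in the Introduction (40.5% and 37.9%).** With R = 4, the averages are 4c/0.405 = 9.9c for IUI and c/0.379 = 2.6c for ICI. Each extra IUI pregnancy costs 3c/0.026 = 115c.

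**Shared costs.** The Interventions section says: "In the ICI cycles, ovulation detection is in the same way as in the IUI arm", so monitoring per cycle is common to both arms and pulls R towards 1. To see the effect, assume 4:1 per cycle for the arm-specific cost, up to six cycles with a constant chance per cycle, stopping at pregnancy, and a common cost of m per cycle (in units of the ICI-specific cost). Break-even for ICI is then:

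| m | 0 | 1 | 2 | 4 | 8 |
|---|---|---|---|---|---|
| Break-even ICI rate | 11.6% | 18.1% | 22.1% | 27.0% | 31.5% |

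Mean cycles per woman are 4.90 at 40% and 5.26 at 28%. At 28%, the per-cycle ratio at which the ranking flips is (5.255/0.28)/(4.901/0.40) = 1.53. Solving (4 + m)/(1 + m) = 1.53 gives m of about 4.6. Below that shared cost, ICI still ranks first at the margin limit; above it, IUI does.

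**Pregnancy costs.** A fixed cost per pregnancy adds the same amount to both averages and to the incremental ratio, so it does not change the ranking.

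**The case against.** The strongest reply is that incremental ratio graphs and acceptability curves are in the plan, and that these are the tools for judging whether IUI is worth its extra cost. A reader might infer from the per-arm sentence that the evaluation cannot answer this question, or that the average ratio is its declared headline. The text supports neither. The incremental tools are named, no measure is given priority, and the link between those tools and the sensitivity analyses is the natural reading but not the only one.

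Three further replies also stand.

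- Where pregnancy rates are close, the cost-minimisation option compares costs directly, so the 115c figure may fall where no average ratio would be used.
- A loss of pregnancies with ICI would not go unseen. The Data analysis section tests ongoing pregnancy on the absolute risk difference and reports relative risks with 95% CIs.
- A reader might infer that the average favours ICI even if most births are lost. That requires an all-in cost ratio above 2:1 per woman. The article does not say whether its fourfold figure is per cycle, per woman or for the procedure alone.

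It can also be said that a condensed article may leave economic detail to a fuller plan. That covers the bootstrap method and the table layout. It does not cover a measure that the article itself states. What remains is that the stated measure does not give the incremental quantity that the Introduction's question calls for.

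**Conclusion.** The point holds as a low-severity improvement. The measure stated for each strategy is a within-arm average. It does not give the cost of an extra pregnancy or birth, and it can rank ICI first at the limit of the non-inferiority margin for any all-in cost ratio per woman above 1.43. With the fourfold ratio assumed per woman, the averages are 3.6c and 10c against an incremental cost of 25c.

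These sizes rest on an IUI rate of 40%, an ICI rate of 28% and an assumed cost ratio. With a large enough shared cost per cycle (above about 4.6 times the ICI-specific cost in the model used here), the ranking at 28% reverses. The evaluation as a whole can still answer the question with the tools already planned, and the trial's primary conclusion does not depend on it.

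**What to change.** Where the cost-effectiveness branch is used, replace the per-strategy sentence with wording such as:

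*The base-case economic result is the difference between IUI and ICI in mean cost per woman, the difference in live births and in ongoing pregnancies per woman, and the incremental cost per additional live birth or ongoing pregnancy. Uncertainty is shown with the incremental cost-effectiveness graphs and acceptability curves. Cost per pregnancy within each arm is descriptive and is not used to rank the strategies.*

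If one arm is both cheaper and more effective, report that directly instead of a ratio.

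The cost is about one sentence of the economic plan. The data are the same and the displays are already planned. The drawback is that the result is less simple to quote than a price per pregnancy.
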